### Economic Analysis

To assess the cost-effectiveness of the intervention, costs per quality adjusted life year (QALY) will be calculated. The analysis will be performed from a societal perspective with a time horizon of one year. Patients will receive a health care resource use questionnaire at 6 months and 12 months. In this questionnaire, a patient will be asked to fill in their total health care utilization, such as outpatient clinic visits, emergency visits, admissions for any reason, and visits to the general practitioner. All outpatient clinic visits, emergency visits, and admissions for any reason reported in the questionnaire will be verified by EMR data. In the same questionnaire, the patient will be asked to fill in total medication use. All health care and medication use will be multiplied with standard cost prices to calculate costs [22]. To calculate indirect costs, patients will be asked to note absence from paid and unpaid work. Productivity costs will be calculated using the friction cost method. Absence will again be multiplied against standard cost prices [22]. QALYs will be calculated from utility scores from the SF-36 questionnaire, which will be administered at baseline, 1 month, 6 months, and 12 months [19,23]. Finally, costs and QALYs in both groups will be compared. It is our hypothesis that societal costs will be lower in the intervention group.

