## Results

### Study Outcomes

The primary outcome of this study is the percentage of patients with normalized BP (defined as SBP <140 mmHg and DBP <90 mmHg), as measured at the 12-month outpatient clinic visit. Secondary outcomes of this study are detailed in Textbox 3.

Secondary outcome measures.The percentage of patients with controlled BP (defined as SBP <140 mmHg and DBP <90 mmHg), as measured at the 3-month outpatient clinic visit.Patient satisfaction, as assessed by the patient satisfaction questionnaire [18].Health care utilization, defined as an outpatient clinic visit, emergency care visit, or admission for any reason. This factor will be measured via questionnaires and verified by EMR data.Major Adverse Cardiac Events (MACEs)a. Death of any causeb. Cardiac deathc. Recurrent STEMId. Recurrent NST-ACSe. Revascularizationf. Hospitalization for heart failureg. Transient Ischemic Attackh. Ischemic strokePropensity of medication adherence, measured by the 8-item Morisky Medication Adherence Scale (MMAS-8) [21].Physical activity, as measured by the iPAQ [20].Quality of life, measured by the SF-36 [19].Percentage of patients in which a previously unknown sustained arrhythmia (>30 seconds) is detected.Cost-effectiveness, expressed as the incremental cost-effectiveness ratio.

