### Statistical Analyses

A power calculation was done using R software [24], which is based on a comparison of two proportions of patients with controlled BP (defined as an SBP of 139 mmHg or less and a DBP of 89 mmHg or less). We hypothesize that in the *The Box* group, 95% of the patients will achieve controlled BP, while in the control group, 75% will achieve controlled BP [25]. For this calculation, an alpha of 0.05, a beta of 0.20, and a margin of 0.07 were chosen, yielding a sample size of 200 patients.

Data will be analyzed according to the intention-to-treat principle. Causes of missing data will be tabulated (Multimedia Appendix 1). The percentage of missing data is expected to be low. Therefore, complete case analyses will be done. Analyses will be based on the missing-at-random assumption. If the percentage of missing values exceeds 7%, multiple imputation will be applied in the analysis of the data.

After finishing the study (defined as the last patient’s last visit), the proportion of patients with controlled BP will be compared with a Chi-square test. Logistic regression might be done if serious imbalances of baseline variables exist, to correct for potential confounding variables. Percentages of patients with controlled BP at three months (secondary outcome 1), and percentages of patients in which a previously unknown sustained arrhythmia is detected, will also be compared with a Chi-square test.

Scores of questionnaires (patient satisfaction questionnaire, MMAS-8 scale, iPAQ questionnaire, and SF-36 questionnaire) and health care utilization will be compared using an independent t-test. Major Adverse Cardiac Events (MACEs) will only be reported. As the study is underpowered, no statistics will be done on MACEs. The numbers will be hypothesis-generating.

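### As written, health care use is counted from questionnaires and the EMR check is applied to reported contacts; no stated step adds unreported contacts or uses the records of patients who return no form

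*Protocol article*

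**What the plan says.** Textbox 3 under Study Outcomes lists the secondary outcome: "Health care utilization, defined as an outpatient clinic visit, emergency care visit, or admission for any reason". On the data source it adds: "This factor will be measured via questionnaires and verified by EMR data". So the questionnaire is the measuring instrument and the EMR is the check.

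The Economic Analysis section sets the timing: "Patients will receive a health care resource use questionnaire at 6 months and 12 months". It then states what is checked: "All outpatient clinic visits, emergency visits, and admissions for any reason reported in the questionnaire will be verified by EMR data". Two further cost inputs are self-reported with no stated check. On medication: "In the same questionnaire, the patient will be asked to fill in total medication use". On productivity: "To calculate indirect costs, patients will be asked to note absence from paid and unpaid work". Visits to the general practitioner are also asked for in the questionnaire and are not among the items to be verified.

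For missing data, the Statistical Analyses section expects little and concludes: "Therefore, complete case analyses will be done". It continues: "If the percentage of missing values exceeds 7%, multiple imputation will be applied in the analysis of the data". Utilization is compared by an independent t-test.

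**The concern.** A check that begins with the reported visits can catch over-reporting. It has no means of catching omissions, because a visit that is not on the form never enters the check. A patient who returns no form has nothing to check, although the hospital may hold a full record of that patient's contacts there.

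Two consequences follow. First, totals can be too low in both arms. Second, the difference between arms can be wrong if one arm reports more completely than the other. The trial is open, and contact differs by design. Box patients have two of four visits by video and are contacted by phone or email when their data show irregularities; controls attend four clinic visits. This makes unequal reporting possible, in either direction.

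What is at stake is the utilization outcome and the cost side of the cost-effectiveness ratio. The authors expect lower societal costs with The Box (Economic Analysis) and utilization that is not higher (Health Care Utilization, in the Discussion). Less complete reporting in the Box arm would favour both expectations; less complete reporting among controls would work against them.

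**Working it through.** The plan gives no figure to reproduce here. The point rests on reading the collection rule, followed by an illustration with assumed inputs.

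**Step 1. What the stated rule does to each type of contact**

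| Contact | Stated handling |
|---|---|
| Outpatient visit, emergency visit or admission, reported | Checked against the EMR |
| The same, not reported on a returned form | No step stated |
| Any contact of a patient who returns no form | No record step stated; complete-case analysis, or multiple imputation above 7% missing |
| GP visit, medication use, work absence | Self-report, no check stated |

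The Textbox 3 wording is more general than that of the Economic Analysis section. The two do not conflict, but Textbox 3 does not supply the step absent from rows 2 and 3.

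**Step 2. What the missing-data rule can repair**

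The 7% threshold corresponds to 0.07 × 200 = 14 patients. Up to that number, patients without a value are left out; above it, their values are imputed. Imputation estimates a count that the hospital record may already hold. It does nothing for an under-reported count on a returned form, because that value is not missing. Non-return may also be related to outcome. The Discussion cites one-year mortality below 10%, that is, fewer than 0.10 × 200 = 20 patients. Those who die cannot return later forms, yet their last admissions may be costly.

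**Step 3. Illustration of size**

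From the article: 200 patients randomised 1:1, so 100 per arm, and a t-test. A two-sided 5% level is used. Assumed, because the article gives no rates: true mean μ = 5 contacts per year and SD 3 in both arms, no true difference, and reporting fractions r₁ and r₂.

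- Spurious difference = μ(r₁ − r₂)
- SE = 3 × √(2/100) = 0.424
- With δ = difference/SE, rejection probability ≈ Φ(−1.96 + δ) + Φ(−1.96 − δ)

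| Assumption | Difference | δ | False-positive rate |
|---|---|---|---|
| Equal reporting | 0 | 0 | 5% |
| 90% v 80%, one of the five contacts forgettable | 1 × 0.10 = 0.10 | 0.24 | about 5.6% |
| 5-point gap, all five forgettable | 5 × 0.05 = 0.25 | 0.59 | about 9% |
| 90% v 80%, all five forgettable | 5 × 0.10 = 0.50 | 1.18 | about 22% |

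A simulation with Poisson counts (4,000 runs, 100 per arm) gives the same pattern. At a true mean of 4, equal capture of 90% in both arms leaves the rate at about 5%; 90% against 80% gives a spurious difference of 0.4 visits and about 33%. The rate is higher than 22% mainly because Poisson counts with mean 4 have an SD of about 2, not 3.

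**The case against.** The strongest reply is that the article condenses a longer protocol, and that verifying a questionnaire against a record may in practice include filling in omissions. This stands in part. A reader might infer that the EMR will be consulted only for reported visits and that everything else is never recovered. The article contains no such exclusion, and Textbox 3 words the check without limiting it to reported visits. What can be said is narrower: the article itself names the instrument and the contacts to be checked, and the method so described has no step for omissions or for non-responders.

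A reader might also infer that non-responders simply drop out. They do so only at or below 7% missing; above it, imputation applies.

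A third tempting reading is that the whole comparison rests on six-month recall. The recall window is implied by the questionnaire dates, not stated. Reported hospital contacts are checked against the record, no-shows at digital and physical clinic visits are monitored (Patient Compliance), and recurrent infarction, revascularization and heart-failure admissions are collected as MACEs. The article does not say that the no-show or MACE data feed the utilization count, but they show that some contacts are known independently of recall.

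Finally, the 22% depends on treating every contact as forgettable. Four contacts per patient are scheduled in each arm (four clinic visits for controls; two clinic and two electronic visits for The Box), and omission of these is less likely to go unnoticed. Nothing in the article shows that reporting differs by arm. Both objections stand, so the 22% cannot be offered as an estimate.

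**Conclusion.** The point holds as a weakness in the stated method for a secondary outcome and for the economic analysis. The method leaves room for under-counting within each arm. Bias between arms is possible but not shown: it requires reporting completeness to differ, and its direction cannot be inferred. Its size is unknown. The illustrative rates, from about 5.6% to 22% with mean 5 and SD 3 and about 33% in one Poisson setting, show only how strongly the t-test result depends on the unverified reporting fractions. The primary blood pressure outcome is not affected. This is a worthwhile improvement, not a serious defect.

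**What to change.** For every randomised patient, as consent allows, extract outpatient, emergency and inpatient contacts from the hospital record over the full year, whether or not the patient reported them or returned a form. Add questionnaire-reported care at other institutions, and use the union for both the utilization outcome and the costs. If a two-way check covering non-responders is already intended, one sentence saying so in Economic Analysis and Textbox 3 settles the point.

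The cost is one extract for about 200 patients from records that the trial already opens for verification. One caution applies: the EMR described under Data Integration in Electronic Medical Records belongs to the cardiology department, while the outcome covers contacts for any reason, so the hospital-wide record may also be needed. Care elsewhere, GP visits, medication use and work absence would remain self-reported.

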### Statistical Analyses

A power calculation was done using R software [24], which is based on a comparison of two proportions of patients with controlled BP (defined as an SBP of 139 mmHg or less and a DBP of 89 mmHg or less). We hypothesize that in the *The Box* group, 95% of the patients will achieve controlled BP, while in the control group, 75% will achieve controlled BP [25]. For this calculation, an alpha of 0.05, a beta of 0.20, and a margin of 0.07 were chosen, yielding a sample size of 200 patients.

Data will be analyzed according to the intention-to-treat principle. Causes of missing data will be tabulated (Multimedia Appendix 1). The percentage of missing data is expected to be low. Therefore, complete case analyses will be done. Analyses will be based on the missing-at-random assumption. If the percentage of missing values exceeds 7%, multiple imputation will be applied in the analysis of the data.

After finishing the study (defined as the last patient’s last visit), the proportion of patients with controlled BP will be compared with a Chi-square test. Logistic regression might be done if serious imbalances of baseline variables exist, to correct for potential confounding variables. Percentages of patients with controlled BP at three months (secondary outcome 1), and percentages of patients in which a previously unknown sustained arrhythmia is detected, will also be compared with a Chi-square test.

Scores of questionnaires (patient satisfaction questionnaire, MMAS-8 scale, iPAQ questionnaire, and SF-36 questionnaire) and health care utilization will be compared using an independent t-test. Major Adverse Cardiac Events (MACEs) will only be reported. As the study is underpowered, no statistics will be done on MACEs. The numbers will be hypothesis-generating.

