## Methods

### Study Design (Design, Randomization, and Follow-Up)

*The Box* is a single-center open RCT, and is a parallel group study. The study will be conducted at the Leiden University Medical Center (LUMC), a tertiary care hospital in Leiden, The Netherlands. The trial is registered under clinical trial number NCT02976376 (Clinicaltrials.gov) and NL56453.058.16 (Toetsingonline.nl). After inclusion, patients will be randomized 1:1 to either *The Box* (intervention group) or to regular follow-up (control group). Block randomization per 10 participants will be performed. Randomization will be stratified per primary diagnosis (STEMI or NST-ACS) and per age (<50, 51-60, 61-70, 71-80, and >80 years). A website will be used to generate randomization lists [16].

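### The sample size is built on a margin of 0.07 that the planned chi-square test does not use, so the stated 80% power is not the power of the planned primary analysis

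*Protocol article*

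**What the plan says.** All the design inputs are in the protocol article, section Statistical Analyses. The assumed rates are that "95% of the patients will achieve controlled BP" in The Box group, "while in the control group, 75% will achieve controlled BP". The remaining inputs and the result are: "an alpha of 0.05, a beta of 0.20, and a margin of 0.07 were chosen, yielding a sample size of 200 patients". Allocation is equal (Study Design: "patients will be randomized 1:1 to either"), so 200 means 100 per arm.

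Further down the same section, the primary analysis is that "the proportion of patients with controlled BP will be compared with a Chi-square test". Study Outcomes gives the endpoint without any threshold for the difference: "The primary outcome of this study is the percentage of patients with normalized BP", measured at the 12-month clinic visit.

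The 0.07 margin is not used again. No hypothesis, confidence-interval rule or success criterion refers to it. The other 7% in Statistical Analyses is the level of missing values that triggers multiple imputation, and is unrelated.

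**The concern.** A margin in a two-proportion sample size shifts the null hypothesis away from zero difference. A chi-square test has its null at zero difference. The trial is thus sized for one hypothesis and analysed under another, and the power quoted for the first does not carry over to the second.

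Two things are at stake. First, the power statement that the ethics committee and readers rely on does not describe the planned analysis. Second, a reader who sees a 7-point margin in the design could take a significant result as evidence of a benefit larger than 7 points. The planned test cannot supply that evidence.

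**Working it through.** **Inputs** (Statistical Analyses and Study Design): p1 = 0.95, p2 = 0.75, difference 0.20, alpha 0.05 with sidedness not stated, power 0.80, margin m = 0.07 with type not stated, 100 per arm. No allowance for dropout is stated. Normal quantiles: 1.645 (one-sided 5%), 1.960 (two-sided 5%), 0.842 (80% power).

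Variance term: 0.95 × 0.05 + 0.75 × 0.25 = 0.0475 + 0.1875 = 0.235.

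**Step 1. Reproducing 200.** For a test that the difference exceeds m, n per arm = 0.235 × (z_alpha + z_beta)² / (0.20 − 0.07)².

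- One-sided 5%: 0.235 × (1.645 + 0.842)² / 0.0169 = 86.0, total 172.
- The same with the continuity correction n' = (n/4) × [1 + √(1 + 4/(n × 0.13))]²: 100.8, so 101 per arm, total 202.
- Two-sided 5%: 0.235 × (1.960 + 0.842)² / 0.0169 = 109.1, so 110 per arm, total 220 (250 with correction).

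Reading the margin as non-inferiority replaces 0.13 by 0.20 + 0.07 = 0.27 and gives a total of 40 (one-sided 5%) or 52 (one-sided 2.5%). Of the test-based readings tried, only the one-sided, continuity-corrected superiority margin comes close to 200.

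**Step 2. The planned test.** Two-sided 5% chi-square, no margin, pooled rate 0.85 under the null:

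- n per arm = [1.960 × √(2 × 0.85 × 0.15) + 0.842 × √0.235]² / 0.20² = 48.8, so 49 per arm, total 98. With continuity correction it is 58.4, so 59 per arm, total 118.
- Power with 100 per arm: (0.20 − 1.960 × √(0.255/100)) / √(0.235/100) = 2.084, which is 98.1%. Exact binomial enumeration gives 98.9% uncorrected and 97.8% continuity-corrected.
- At 90% v 75%, exact power with 100 per arm is 81.6% uncorrected and 75.2% corrected.

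**Step 3. Margin test at N = 200.** 0.13 / √(0.235/100) = 2.682.

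- Two-sided 5%: 2.682 − 1.960 = 0.722, power 76.5% (exact Wald 77.1%).
- One-sided 5%: 2.682 − 1.645 = 1.037, power 85.0% (exact Wald 85.7%).

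**Step 4. What a significant chi-square would show.** Suppose 75 of 100 controls are controlled.

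| Criterion | Smallest count in The Box arm | Observed difference |
|---|---|---|
| Chi-square, uncorrected | 86/100 (p = 0.0496) | 11 points |
| Chi-square, continuity-corrected | 87/100 (p = 0.047) | 12 points |
| Lower 95% CI bound above 0.07 (Wald) | 93/100 (z = 2.19; 92/100 gives 1.957) | 18 points |

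If the true difference were exactly 7 points at the assumed control rate (82% v 75%), the chi-square would be significant in 23% of trials uncorrected and 18% corrected. These are not type I errors of the planned test. They show only that a significant result does not establish a benefit above 7 points.

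**The case against.** The strongest reply is that nothing is wrong with the planned analysis. The Introduction hypothesizes improvement, the Discussion speaks of better control of parameters such as blood pressure, and a chi-square test of no difference fits both. The document claims no benefit above 7 points. The planned test has far more than 80% power at the assumed rates, and its type I error is unaffected. All of that stands. It rules out two stronger inferences that a reader might draw: that the trial is underpowered, and that success has been defined as more than 7 points. The 77% power figure applies only to a two-sided margin test, which the article does not plan.

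A second reply is that calling 0.07 a superiority margin is an inference. That is correct, because the article says only "a margin of 0.07 were chosen". Other routes also lead to 200. A 95% CI half-width of 0.07 around a rate of 0.85 needs 1.96² × 0.85 × 0.15 / 0.07² = 99.96, so 100 per arm. Also, 172 inflated for 14% dropout is 172 / 0.86 = 200. The first makes no use of beta and does not fit a comparison of two proportions. For the second, no dropout allowance is stated. Neither makes 80% the power of the chi-square test. It also follows that 200 cannot be called a miscalculation, since at least one formula nearly reproduces it.

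A third reply is that a journal article may leave sidedness and the form of the chi-square test to a fuller document. That excuses the missing detail. It does not reconcile a margin-based sample size with a no-margin test when the article states both.

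**Conclusion.** The point holds as a misstated power and sample-size basis. The article attaches 80% power to 200 patients through a margin of 0.07, while the planned two-sided chi-square test has about 98-99% power with 100 per arm and needs about 98 patients (118 continuity-corrected) for 80%. The best-supported origin of 200 is a one-sided 5% superiority-margin test with continuity correction (202), but the article does not say so.

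The validity of the planned test is not threatened, and power is not lacking under the assumed rates. The consequence is that the design basis is wrong as written, and that a significant chi-square result would not demonstrate a benefit above 7 points.

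These figures assume 95% v 75%, two-sided 5% where the chi-square is concerned, and 100 evaluable patients per arm. With 90 per arm, the uncorrected chi-square still has 97.9% power by exact enumeration. The figures at 90% v 75% and the 11- or 12-point threshold depend on whether a continuity correction is used, which the article does not state.

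**What to change.** Keep 200 patients and the chi-square test. Delete the margin from the sample-size paragraph and restate the power for the planned test: with 100 evaluable patients per arm and two-sided 5%, about 98-99% for 95% v 75%, and for 90% v 75% about 82% uncorrected or 75% continuity-corrected. State which form of the chi-square test is used, and report the risk difference with its 95% CI beside the p-value, so that readers can judge the size of the benefit.

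Only if a benefit above 7 points is truly intended should the margin stay. In that case, name its type and sidedness, make a lower 95% CI bound above 0.07 the primary criterion in place of the chi-square test, and state the power as about 77% at 200 patients. Reaching 80% on that criterion would take 220 before any losses.

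The first option costs a rewording of the sample-size and primary-analysis paragraphs and no extra patients. The second changes the primary criterion and accepts lower power or 20 more patients. Either choice should be made before outcome data by arm are seen.

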### Clinical Effectiveness

It is expected that with daily monitoring of ECG, BP, weight, and steps, data will allow for early detection of high BP and the development of arrhythmias. For this study, the percentage of patients with controlled BP at 12 months has been chosen as primary outcome. Controlled BP is associated with lower risks of death, recurrent PCI, and stroke in patients who suffered from ACS. Therefore, the European guidelines recommend tight BP control via medication and lifestyle advice.

Percentages of 1-year mortality after STEMI or NST-ACS vary, but have been reported to be under 10% [26]. With a sample size of 200, it is expected that this study is underpowered to detect a significant difference in mortality between the intervention group and control group. It is emphasized that it is not the primary objective of this study to demonstrate a difference in mortality. This study is intended to investigate whether regular monitoring of clinical parameters (including BP) can lead to better control of those parameters, therefore improving surrogate outcomes in these patients.

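### The primary test uses complete cases until missing values pass 7% of an unstated denominator, which the stated missing-at-random assumption does not in general justify

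*Protocol article*

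**What the plan says.** The protocol article fixes the missing-data rule itself, under Statistical Analyses, after stating an intention-to-treat analysis and a tabulation of the causes of missing data. The default is: "The percentage of missing data is expected to be low. Therefore, complete case analyses will be done". The assumption is: "Analyses will be based on the missing-at-random assumption". The exception is: "If the percentage of missing values exceeds 7%, multiple imputation will be applied in the analysis of the data". It does not say whether the 7% refers to the whole trial, to each arm or to each variable.

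The primary test is a chi-square test of the proportion with controlled BP at the 12-month clinic visit. Logistic regression is optional and tied to serious baseline imbalance.

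Three other places bear on the rule:

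- Study Withdrawal allows patients in The Box to be withdrawn for nonadherence, with no counterpart in the control arm. Nonadherence says that such patients are not excluded and stay in follow-up.
- Clinical Effectiveness says of deaths: "Percentages of 1-year mortality after STEMI or NST-ACS vary, but have been reported to be under 10" per cent. Nothing says how a patient who dies before month 12 enters the primary percentage.
- The 3-month and 12-month visits are clinic visits in both arms. Only the 1-month and 6-month visits become electronic in The Box.

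**The concern.** First, the assumption and the test do not match. Missing at random lets missingness depend on anything observed, such as age, diagnosis or the 3-month BP. The unadjusted chi-square on complete cases conditions on arm alone. If patients with a high 3-month BP are more often lost and less often controlled at 12 months, the data can be missing at random while the observed percentage in that arm is still too high.

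Second, the primary method turns on a percentage that is known only as data accrue, in an open trial where the count can be seen by arm. On an overall reading, 14 missing patients (7.0%) give complete cases and 15 (7.5%) give imputation. Without a denominator, the same data could be held to fall on either side.

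Third, missingness may differ between arms, because withdrawal for nonadherence exists in The Box only. If patients who disengage from monitoring are less often controlled, dropping them flatters The Box. At stake is the size of the primary treatment difference and, for uneven losses, whether the test is significant.

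**Working it through.** **The plan's own figure.** The plan states "an alpha of 0.05, a beta of 0.20, and a margin of 0.07 were chosen, yielding a sample size of 200 patients". The assumed rates are "95% of the patients will achieve controlled BP" for The Box and "in the control group, 75% will achieve controlled BP". One variant comes close to 200: superiority by a margin, one-sided 0.05, with a continuity correction.

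- Effect beyond the margin: 0.20 − 0.07 = 0.13.
- n per arm = (1.645 + 0.842)² × (0.95×0.05 + 0.75×0.25) / 0.13² = 86.0.
- With the continuity correction: (86.0/4) × [1 + √(1 + 4/(86.0×0.13))]² = 100.8, so 101 per arm and 202 in total.

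The article states neither the sidedness nor the correction. The figure serves here only to support 100 per arm, which also follows from 200 patients randomised 1:1.

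**Inputs.** 100 per arm; 95% and 75% controlled among patients with a 12-month BP. The control rate among missing patients is not in the document, so a range is shown.

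**Formula.** With m the share missing in an arm, bias of that arm's percentage = m × (rate in observed − rate in missing). Bias of the difference = Box bias − control bias.

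| Missing, Box / control | Controlled among missing, Box / control | Box bias | Control bias | Bias of difference |
|---|---|---|---|---|
| 7 / 7 | 75% / 55% (20 points lower) | 1.4 | 1.4 | 0 |
| 7 / 7 | 47.5% / 37.5% (half) | 3.3 | 2.6 | 0.7 |
| 7 / 7 | none | 6.65 | 5.25 | 1.4 |
| 7 / 0 | 75% | 1.4 | 0 | 1.4 |
| 7 / 0 | none | 6.65 | 0 | 6.65 |
| 10 / 4 | 75% / 55% | 2.0 | 0.8 | 1.2 |
| 10 / 4 | none | 9.5 | 3.0 | 6.5 |
| 14 / 0 | 75% | 2.8 | 0 | 2.8 |
| 14 / 0 | 50% | 6.3 | 0 | 6.3 |
| 14 / 0 | none | 13.3 | 0 | 13.3 |
| 0 / 14 | none | 0 | 10.5 | −10.5 |

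For example, 0.14 × (0.95 − 0.50) = 6.3 points and 0.07 × (0.95 − 0) = 6.65 points. The rows with 7 stay below the trigger on either a per-arm or an overall reading. The rows with 10 or 14 do so only on an overall reading (14/200 = 7.0%). Positive values favour The Box; losses concentrated in control work the other way.

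The small result for balanced losses needs both arms' missing patients to be informative in the same direction. If, at 7% per arm, none of the missing were controlled in The Box and all were in control, the bias would be 6.65 + 1.75 = 8.4 points.

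**Effect on the test, worst case.** With 14 missing in The Box, complete cases give 82/86 v 75/100, p = 0.0001. Counting the 14 as not controlled gives 82/100 v 75/100, p = 0.23 (both without continuity correction). Imputation would not have been triggered on an overall reading.

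**Deaths and the trigger.** If deaths count as missing values and the 7% is overall, the binomial probability of more than 14 deaths in 200 is 8% at an assumed mortality of 5%, 43% at 7% and 80% at 9%. All three are compatible with a mortality under 10%, so deaths alone could select the method.

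**The case against.** The strongest reply is that the threshold is prespecified, low missingness is a reasonable expectation with a clinic visit in both arms at month 12, and a count of missing values can be taken without comparing outcomes. Balanced losses do little harm. At the planned effect, the moderate scenarios also leave the test significant: about 92 v 75 and 89 v 75 per 100 give p of about 0.001 and 0.01. All of this stands. It limits the size of the problem, but it does not repair the mismatch between assumption and test or supply the denominator.

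A second reply is that imputation details belong in an analysis plan that is not shown. That holds for predictors and software. It does not hold for the default, the assumption and the trigger, which the article fixes itself.

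Several stronger readings are tempting and are not supported:

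- That the 7% is pooled over both arms. The text gives no denominator, so the 14-to-0 case applies on one reading only.
- That the complete-case test is always invalid under missing at random. If missingness depends on arm alone, it is valid.
- That the method is chosen after unblinding. The trial is open, so there is no unblinding; the point is only that the count can be seen by arm.
- That the article cites mortality of up to 10%. It says under 10%.
- That a BP will be imputed for patients who have died. The article neither says so nor rules it out, and the appendix with the table of causes is not shown.
- That deaths bias the result. With 7 deaths in The Box and 3 in control, 0.93×0.95 − 0.97×0.75 = 15.6 points, against 20 among survivors. That is a different estimand, not the correction of an error.
- That imputation would cure informative dropout. Under missing at random it would not.

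**Conclusion.** The point holds in a limited form. The stated rule pairs a missing-at-random assumption with a test that generally needs more than that assumption, and it switches the primary method at a 7% that has no denominator. At the planned rates and 100 per arm, balanced and similarly informative losses bias the difference by at most 1.4 points. Several points require losses concentrated in one arm and a clearly lower control rate among those lost. The Box-only withdrawal rule makes concentration there possible, but the document does not show that it will happen: the Nonadherence section keeps these patients in follow-up, and the two passages conflict. The sizes rest on assumed control rates among missing patients, so they show what the rule would let through and do not forecast the result. The change is worth making before analysis because it is cheap and the better method uses data already planned in both arms.

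**What to change.** - Delete the 7% trigger. For missing 12-month BP in surviving patients, use multiple imputation by arm at any level of missingness, with diagnosis, age group and the 3-month clinic BP as predictors.
- Keep complete cases as a sensitivity analysis. Add a tipping-point analysis that lowers the control rate among missing patients, separately by arm, until the conclusion changes.
- Do not impute a BP for patients who died. State in advance how they enter the primary percentage, and show the alternative (for example, counted as not controlled) as a sensitivity analysis.
- Reconcile Study Withdrawal and Nonadherence on whether nonadherent Box patients are withdrawn.

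The cost is wording and a modest amount of programming. The primary comparison becomes a difference in proportions pooled over imputations instead of a single chi-square table. No visit or measurement is added.
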